# STUDY BACKGROUND

In contrast with the wealth of observational data supporting the hypothesis that health and

wellbeing in later life are influenced strongly by behavioural factors and social conditions, there is a dearth of evidence about interventions that are effective in promoting improved health and wellbeing in later life. Prerequisites for the development of such interventions include identification of: i) intervention modalities that are expected to be effective, culturally appropriate and cost effective; ii) windows of opportunity when interventions are likely to be most effective; and iii) outcome measures that are responsive to the interventions and can measure change in health and wellbeing. Life stage transitions involve changes in lifestyle and thus present key opportunities for behaviour change interventions; the LiveWell research programme aims to develop evidence-based, acceptable and scalable interventions to improve health and wellbeing in the retirement transition.

This programme of research follows the MRC framework for the development and evaluation of complex interventions (Craig et al, 2010). First, we systematically reviewed the effectiveness of interventions to change key health behaviours and social factors of people in the retirement transition. We have found that interventions with people of retirement age can effectively promote components of the Mediterranean diet (Lara et al, unpublished), physical activity (Hobbs et al, 2013) and explicit social roles (Heaven et al, 2013). We have also identified the intervention modalities and intervention content (behaviour change techniques; Michie et al., 2011) associated with intervention effects. We have also conducted qualitative research with people in the retirement transition to explore how wellbeing is defined and how best to intervene to promote health and wellbeing. Second, using co-design methods (Bate & Robert, 2007; NHS Institute for Innovation and Improvement, 2009) with intervention stakeholders (older adults as potential intervention users, intervention providers or commissioners), we integrated the evidence from the systematic reviews and qualitative research to develop and prototype new intervention ideas. In collaboration with a digital marketing and design company (Hippo Creative and Cloud Data Service), a web-based intervention platform has been developed using an iterative design and development process. Potential intervention users have been involved at all stages using co-design methods, providing information on intervention feasibility, acceptability and usability. The final intervention is called LEAP “living, eating, activity and planning through retirement”, and will now be formally tested for feasibility and acceptability in a pilot randomised controlled trial (RCT). This trial will be registered with International Standard Randomised Controlled Trial Number Register (ISRCTN).

## The LEAP intervention

LEAP is a web-based intervention using a responsive design so that it can be accessed on a PC, tablet or mobile phone. The intervention comprises five modules of tools, activities and resources for the intervention user. There are also sections for user registration, LEAP overview, user diary and user dashboard. The intervention content that is presented is personalised to the user on the basis of the information they provide at different stages. The user determines the route they take through the intervention, choosing which modules to complete in what order, and skipping or revisiting modules as desired. However, the intervention uses information about the user’s individual needs and situation to make suggestions about which modules may be most beneficial for the user. Thus, each user’s experience of the intervention is tailored to their preferences.

### Virtual Mentor

As part of the co-design phase, we explored what an intervention for people in the retirement transition could look like and how it could be delivered. A priority for the research team was to develop a digital-based intervention which may be more compatible with modes of accessing information in future cohorts of older people (e.g. by smart phone) rather than traditional paper and pencil methods. A digital intervention also has greater potential for wide-scale use in the target population. A web-based intervention was seen to be an acceptable mode of delivery by older adults. Some older adults emphasised that a web-based intervention would allow them to access the intervention in their own homes and at a time convenient to them. However, the potential risks associated with a web-based intervention were also expressed; some older adults felt that they might not engage with a website and feel unsupported. Older adults in the co-design workshops identified that having access to a mentor could help to explore retirement transition options and lifestyle behaviours. In order to produce a cost-effective, digital-based intervention, the research team developed a range of ‘virtual mentors’ to guide intervention users through the website. The idea of a virtual mentor was developed further and tested by older adults. The mentoring feature was found to be useful.

When the user registers with LEAP they are invited to choose a mentor to guide and support them through the intervention. There are eight animated mentors to choose from; four males and four females, each of whom is presented alongside their brief personal background. The mentor ‘speaks’ to the user as they move through the intervention, explaining the purpose of each module and activity, providing instructions and directing them to resources. A user can choose to mute the mentor’s voice and just read instructions if they prefer.

### LEAP modules and features

1. The ‘registration’ section is applicable when the user first accesses LEAP. This module includes a sign up page and a short registration questionnaire about retirement status (fully retired, semi-retired or not yet retired), and feelings about physical activity, dietary behaviours, and social relationships.
2. The ‘LEAP overview’ section provides the user with an overview of the objectives of each module and guidance on the general functions and features of LEAP, including the ability to choose and subsequently amend personal preferences.
3. The ‘Time’ module encourages the user to reflect on how they spend their time currently and how they would like to at a later stage in their retirement transition. They are asked to think specifically about time spent working, caring for others, pursuing hobbies, being physically and socially active, doing household duties and having undefined ‘free time’. Although reflection on the use of time was not initially a target for the LiveWell programme, analysis of the qualitative data indicated that assistance with reflecting on current and future time use was important for people within the retirement transition, especially with regard to thinking through the possibilities for various lifestyle behaviours, goals and aspirations. The format of this module was developed further through the co-design workshops to include a user-friendly graphical display of time use.
4. The ‘Changing Work’ module allows the user to consider their financial and work situation as they move through the retirement transition. Users who are not fully retired (working full or part time) can explore whether they can afford to retire when they would like to or whether reducing their working hours would be a possible solution. Users who have already retired may consider their income and expenses and whether they would like to look for part-time work or start their own business. The module uses a range of tools including calculating cost of living, likely income and expenditure, and displaying the results in graphical formats. The tool prompts the user to consider the contribution of their state pension and bus pass and states when these are applicable given current legislation and the user’s date of birth and gender. There are also useful links to external resources for the user to access for a more detailed personal assessment. Like the ‘time’ module – work transitions were not originally a target for intervention in LiveWell. However analysis of our qualitative data indicated that finances and modes of work transition shaped how people experienced retirement, and set the conditions for lifestyle behaviours.
5. The ‘Moving More’ module supports the user to move more and sit less. Users are provided with a pedometer at the beginning of the intervention to measure their step count. The module encourages the user to self-monitor their daily step count and to set daily step goals. The user is prompted to set outcome goals for being more active (i.e., lose weight, feel happier etc.) and to explore different ways of being more active. The user can schedule when they will be more active in a diary, explicitly stating when, where and with whom they do a particular activity (i.e., action planning). Finally the user is presented with potential barriers to doing the activities they have said they would like to and encouraged to identify potential solutions to the problems. The user is reminded to regularly return to this module to update their daily step count, review their goals, schedule new activities and reconsider the barriers and solutions to being more active. The user can share what they have done in this module via email, Facebook or twitter, and can print a summary to serve as a reminder for themselves.
6. The ‘Being Social’ module explores the potential benefits of having a meaningful occupation or role and spending time with friends, family and work colleagues. In the social roles tool the user is asked if they would like to consider paid, unpaid or both forms of work and is provided with some case studies to help them consider their preferences. If the user chooses paid work they are reminded to explore the ‘work transitions’ module but are also given links to relevant external sites (e.g. business link). If the user selects non-paid work they complete a brief questionnaire designed to stimulate reflection on the type of role that the user might pursue and to elicit information regarding occupation or role preferences. The user is prompted to print their list of role preferences and is then presented with links to relevant external organisations that offer volunteering placements. In the social relationships tool, the user is prompted to explore the relationships that are important to them which are mapped out visually. The user is then prompted to think how these relationships might change through the retirement transition, and to add any additional relationship ‘types’ (e.g. to make new friends) that they might want to develop in the future. The tool helps the user to identify opportunities to develop these relationships through several tools. In the first instance the user is invited to enter individual names within each relationship category to help personalise later steps in the module. The tool then presents a list of potential social activities for each relationship type, which can be filtered based on preferences of cost, accessibility (e.g. for young children or people with limited mobility), and intensity (level of physical activity involved). The activities presented by the tool are those that suit the particular relationship type currently selected by the user (e.g. grandchildren). The user can save activities for later consideration, or add activities (with specific individuals or as relationship type) to their diary explicitly stating when, where and with whom they do a particular activity (i.e., action planning).
7. The ‘Eating Well’ module encourages the user to consider their current diet and explore ways in which it might be changed to correspond more closely to a Mediterranean-style eating pattern. Initially, users are invited to respond to a 14-item validated questionnaire designed to capture key facets of their current diet in relation to the principles of Mediterranean eating (Martinez-Gonzalez et al, 2012). They then receive brief feedback specifically tailored to the questionnaire items on which they did not score optimally. Users have the chance to prioritise and refine the feedback further before receiving ideas for meals (snacks, drinks, breakfast, light meals and main meals) that put the feedback into practice. Users can filter the meal ideas they view by dietary preference, cost, cooking skills and time. They have the opportunity to save meal ideas in a virtual ‘recipe book’ if they would like to try them, and they are encouraged to add meal ideas to their diary, stating when, where and with whom they will eat. Users are also prompted to reflect on the goals they would like to achieve by eating better; they are further prompted to consider barriers that may obstruct their efforts to put into practice the feedback they have received. Upon exiting the module, they receive a reminder of the feedback they received and the outcome goals they identified.
8. The ‘diary’ section presents the activities that the user has scheduled for the current week and the following week. This information can be downloaded to the user’s computer calendar or printed.
9. The ‘dashboard’ section presents a summary of the activities, tools and resources the user has engaged with or has saved to view later. It prompts the user to revisit modules to report on the activities they have engaged with, revise their goals, schedule new activities etc.

### Notifications

In the ‘LEAP overview’ section, users will be asked to opt-in to receive via email a weekly bulletin summarising the information that is displayed on their dashboard. This bulletin will act as a prompt for the user to revisit LEAP and engage further with the modules. Users can amend whether they receive this bulletin or not at any time by modifying their personal preferences.

## Healthy Ageing Phenotype

The lack of outcome measures which capture the essential components of the healthy ageing phenotype (HAP), as distinct from measuring disability or ill-health, is a significant impediment to the evaluation of interventions in this area. In this programme of research we have defined a suite of outcome measures, including relevant biomarkers, and identified tools appropriate for capturing the HAP (Lara et al, 2013). We have selected a subset of these measures and tools that may be appropriate to use in a pragmatic RCT with long-term follow up. The feasibility and acceptability of these measures has yet to be determined and therefore will be formally assessed in this pilot RCT alongside more proximal outcomes of the intervention modules (i.e. diet, physical activity and social roles).

# SCIENTIFIC RATIONALE and research aims

Before commencing an appropriately powered RCT of the LEAP intervention including an assessment of the HAP, information is needed about the number of eligible participants and the rates of recruitment, retention and data completion. This information will help establish if LEAP will be used by older adults and whether the HAP outcome measures are fit for purpose.

## **Research Aims**

To provide early markers of how the intervention is used, data on physical activity, dietary and social factors, and variability of response to LEAP in order to inform effect and sample size estimates. Qualitative methods will capture additional information including reasons for participation, willingness of participants to be randomised to the intervention, acceptability of data collection and reported use and acceptability of the intervention. The pilot trial will also collect information on the acceptability, feasibility and compliance with the HAP battery assessment procedures.

# STUDY DESIGN

This study is a pilot, individual randomised, single blinded, controlled trial of a web-based lifestyle intervention for people in the retirement transition versus a minimal intervention comparator. Embedded in the trial design is a qualitative process evaluation and an assessment of feasibility and acceptability of a battery of HAP outcome measures.

A total of **90** participants will be recruited and participants will be randomly allocated to one of two conditions:

1. LEAP intervention
2. Minimal intervention control comparator

An allocation ratio of 2:1 will be used for the intervention group compared to the control comparator group.

## LEAP intervention

A total of **60** participants will be randomised to receive the LEAP intervention. Thirty participants are usually sufficient for feasibility testing of an intervention (Lancaster et al, 2004); however, LEAP is a personalised intervention with diverse modules, tools and activities that are tailored to the needs and desires of the user at their individual stage in the retirement transition. The number of potential routes through LEAP and the heterogeneity of the target population are therefore substantial, and thus we will allocate more participants to receive LEAP compared to the control comparator.

## Control Comparator

A total of **30** participants will be randomly allocated to the control comparator which will involve them being emailed a direct link to the NHS choices ‘LiveWell’ website (http://www.nhs.uk/LiveWell/Pages/Livewellhub.aspx). The email will encourage the participants to access the health resources and information on the pages labelled *men’s health 40-60, men’s health 60-plus, women’s health 40-60, women’s health 60-*plus, as appropriate.

## Randomisation

Method of randomisation

Eligible participants will be randomly assigned (in ratio of 2:1) to either LEAP or Control. Randomisation will be undertaking with randomly chose randomisation blocks (3, 6, 9) to maintain balance. All personnel and participants will be blinded to treatment allocation; only a member of the team not involved in aspects of assessment or interventions will have access to treatment allocation. Length of follow-up

This is a pilot feasibility trial and one of its objectives is to collect data about the number of eligible participants and the rates of recruitment, retention and data completion. Study attrition is largely seen within the first month of a trial, therefore we will have a two month follow-up from the start of the intervention, which will give a good indicator of likely attrition in a future definitive RCT with a longer follow-up. We will also collect data on dietary patterns, physical activity and social relationships to identify variability in response to the intervention. The trial is not powered to detect change in these variables in response to the intervention, thus, adopting a longer follow-up period of six or 12 months in order to examine behavioural maintenance is not required. The behavioural data will however be used to inform effect and sample size estimates for a future definitive trial. Figure 1 illustrates participant flow through the trial in accordance with the CONSORT guidelines.

[figure not shown]

**Fig 1. CONSORT 2010 RCT flow diagram**

# Research questions

This pilot trial addresses the following specific research questions:

## Recruitment and retention

1. What is the trial recruitment rate? (i.e., what percentage of people eligible to take part, in the specified geographical location, accepts the invitation to participate)?
2. What percentage of participants are recently retired compared to the percentage that are not yet retired?
3. Does the recruitment strategy result in the successful inclusion of participants from blue collar, manual or physical labour occupational backgrounds?
4. If the recruitment strategy via the community is adopted, in addition to the strategy via employers (see Section 5), then do the recruitment rate and the characteristics of the recruited sample differ for each strategy?
5. What is the trial retention rate? (i.e., what percentage of participants from each intervention arm remains in the trial at each follow-up assessment point?)

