# STUDY Procedure

This pilot trial will work through the following steps:

1. The trial administrator and (where appropriate) collaborating Health Improvement Specialists will contact Human Resources departments of local businesses to ask them if they would be willing to advertise the study to their employees or constituents (email, letters, posters in workplace etc) and where appropriate, contact individual employees or members of the organisation directly (e.g. personalised e-mail). If recruitment is also conducted in the community (e.g. in order to recruit people who have retired) then we will also contact community organisations of older adults and display posters in locations that may be frequented by people living in low socio economic neighbourhoods (more likely to have retired from blue collar or manual occupations rather than managerial or professional roles), and which aren’t linked specifically to existing membership or engagement with routine physical activity (e.g. sports centres). Our strategy therefore will be to display posters in low SES wards in Newcastle (e.g. Benwell, Elswick ) in the following locations: pubs; working men’s clubs; libraries; Citizen Advice Bureaus; supermarkets; noticeboards in religious buildings (e.g. churches, mosques) and shop windows.
2. Potential participants who are interested in participating will be asked to make contact with the trial administrator or to agree for the Human Resources department or community organisation to pass on their details to the research team who will then contact the potential participant directly.
3. The trial administrator will contact the Human Resources departments and community organisations in one week if there has not been any contact.
4. Over the telephone, a member of the research team will assess the potential participants for eligibility using the defined inclusion and exclusion criteria.
5. Eligible participants will be emailed or sent a study invitation letter, a participant information sheet and a consent form. They will be informed that one of the study team will make contact with them in the next five working days to discuss their participation in the study and to answer any questions.

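### The recruitment rate is defined on all eligible people in the area, but the procedures count only eligible people who have already come forward, so the reported rate cannot measure reach or compare it between routes

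*Protocol*

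**What the plan says.** Protocol, Research questions, Recruitment and retention, question 1 defines the trial recruitment rate as "what percentage of people eligible to take part, in the specified geographical location, accepts the invitation to participate". Question 4 in the same list asks whether that rate, and the characteristics of the sample, differ between employer and community recruitment if the community route is opened. The section on scientific rationale gives the purpose: before a powered trial, "information is needed about the number of eligible participants and the rates of recruitment, retention and data completion".

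The STUDY Procedure section sets out how people enter:

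- **Step 1, employers and organisations.** HR departments are asked whether they are "willing to advertise the study to their employees or constituents (email, letters, posters in workplace etc"). Where appropriate, the team may also "contact individual employees or members of the organisation directly (e.g. personalised e-mail").
- **Step 1, community (only if needed).** Older people's organisations are contacted, and "Our strategy therefore will be to display posters in low SES wards in Newcastle".
- **Step 2.** "Potential participants who are interested in participating will be asked to make contact with the trial administrator"; alternatively, they may let HR or a community organisation forward their details.
- **Step 4.** Eligibility is assessed by telephone.
- **Step 5.** "Eligible participants will be emailed or sent a study invitation letter".
- **Step 6.** A call establishes whether each of these people accepts.

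The Participant Recruitment section sets a target of 90 and a window of three months, ending earlier if the target is met.

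**The concern.** The definition and the procedures use different populations. Question 1 takes eligible people in a location as its denominator. The procedures learn whether someone is eligible only after that person has shown interest.

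The missing step is the move from being eligible and reached to making contact. A definitive trial needs that information to judge how many employers to approach and how widely to advertise. If acceptance among volunteers is reported as the recruitment rate, readers may take it as uptake in the target population. The comparison in question 4 would have the same gap: a route that reaches few people and a route that reaches many could show the same acceptance.

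An analysis plan cannot repair this afterwards. The number of e-mails or letters sent and the source of each enquiry have to be recorded while recruitment is under way.

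**Working it through.** The protocol states no expected recruitment rate, no eligible population and no number approached, so there is no figure of its own to reproduce. The only related figure is the target, which is consistent with its arms: 60 + 30 = 90.

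**Where could each count arise?**

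| Quantity | Needed for | Recorded by a step in the text? |
|---|---|---|
| E: eligible people in the location | question 1 as worded | No. The location is not delimited beyond the region, with Newcastle wards named for posters |
| C: people contacted by letter or e-mail | a rate per person approached | Countable in principle; no step says it is kept |
| V: people found eligible by telephone and invited | acceptance among volunteers | Yes, steps 4 and 5 |
| A: people accepting | numerator | Yes, step 6 |

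C is not a substitute for E. Under the Inclusion Criteria, eligibility depends on recent retirement, reduced hours in anticipation of retirement, or a personal plan to retire within two years. An employer's mailing count does not show the last of these.

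V is itself provisional. The paired associates learning test is an exclusion criterion, but Appendix A describes it as a touchscreen test in the assessment battery, so some people invited as eligible may be excluded later.

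**How the two rates relate.** Take everyone in V to belong to E:

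- rate obtained = A / V
- rate defined = A / E = (A / V) × (V / E)

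The factor V / E is the share of eligible people who come forward and pass the telephone screen. That is reach, and no step observes it. For question 4 the same identity holds within each route. Comparing A / V between routes omits both V / E terms, so it can show no difference, or even the opposite order, when reach differs.

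**Illustration with A = 90.** All denominators below are assumptions; none is in the protocol.

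| Denominator | Assumed size | 90 / size |
|---|---|---|
| V | 100 | 90% |
| V | 150 | 60% |
| V | 180 | 50% |
| E | 1,000 | 9% |
| E | 2,000 | 4.5% |
| E | 5,000 | 1.8% |
| E | 10,000 | 0.9% |

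The closest pair in these ranges differs by 50 / 9 = 5.6-fold and the furthest by 90 / 0.9 = 100-fold. The width of that interval shows how little the protocol fixes.

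**What is available in any case.** If the target is met exactly at three months, recruitment runs at 90 / 3 = 30 per month. Because recruitment stops at 90, the numerator may be capped by design. Recruits per unit time is then more informative than a percentage.

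**The case against.** The strongest reply is that question 1 can be read narrowly. It speaks of accepting an invitation; step 5 issues an invitation and step 6 asks for acceptance in nearly the same terms. On that reading the rate is acceptances over people invited, both are observed, and the location phrase only names the catchment. This stands as far as computability goes. A reader might infer that no recruitment rate can be calculated at all, and the document does not support that. But the narrow reading gives exactly the volunteers-only rate and sets aside the location wording, so the wording still has to change.

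Other points on that side:

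- **Recruitment is not only adverts and self-referral.** Direct contact is allowed, and letters and e-mails can be counted. True, and it makes the fix feasible. The route is optional, however, and no step keeps the count.
- **Fig 1, the CONSORT flow diagram, is not shown in the text reviewed, and the Length of follow-up text lists the number of eligible participants among the data to collect.** The figure may track more counts than the text does. A usual box for people assessed for eligibility would still contain only those who came forward.
- **Acceptance among volunteers need not be high.** A reader might assume that it will be, but the protocol gives no such rate. It describes two assessments of about two hours each, seven days of monitor wear and three dietary recalls, and it plans interviews with people who decline. The claim that matters is only that this rate does not measure reach.
- **Source of recruitment is partly covered.** Recruitment pathway is a criterion for qualitative sampling, so it must be known for participants. That does not extend to people who enquire and do not join.
- **Question 4 also compares sample characteristics.** That part is unaffected.

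**Conclusion.** The point holds. As written, question 1 names a denominator that no visible step counts, and the procedures deliver only acceptance among telephone-screened eligible volunteers. That rate does not describe reach and cannot compare the reach of the two routes in question 4. Randomisation and participants are unaffected; what suffers is one of the pilot's main feasibility outputs. It should be corrected before recruitment starts, because numbers approached are hard to recover later.

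The size of the discrepancy cannot be derived from the protocol. A reader might take a fold difference from the illustration and apply it to the definitive trial's recruitment plan; that does not follow, since every denominator there is assumed. Nor is the planning of time lost, because recruits per month can be obtained however question 1 is worded.

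The conclusion rests on the text of the protocol alone, without Fig 1 and without a statistical analysis plan.

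**What to change.** Redefine question 1 on denominators that will be observed:

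- **Employer route.** Report consents per person contacted wherever e-mails or letters can be counted, with each HR contact or organisation supplying the number sent. Add recruits per employer and per week. A count of staff in an age band may be added if it is labelled as a proxy for eligibility.
- **Community poster route.** Report enquiries and recruits per site or organisation and per week, with no population percentage.
- **Acceptance among screened-eligible volunteers.** Keep it, under that name, as a separate result.
- **Enquiry log.** Record the referral source for everyone who makes contact, not only for those who join.
- **Question 4.** Compare routes on recruits per unit time, shown by retirement status. The community route opens only if recently retired people prove hard to recruit through employers, so the mix by retirement status may differ by design. Count time for each route from the date it opens.

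The cost is one count requested from each HR contact or organisation and one field on the enquiry log. The reported rate may look lower than acceptance among volunteers.
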